Among the 13 study EDs, eight functioned as four operational dyads, pairs of EDs, each served by one shared staff of emergency physicians. Keeping these EDs paired, we had nine study clusters, which the principal investigator allocated to one of nine sequences using a computer-generated randomization sequence. Site leads were not blinded to their launch month as they needed to schedule educational presentations. Physicians in study EDs could not be blinded to interventions; patients, however, were unaware of the trial. After an initial period of three months in which all clusters were in the control condition (July 2021 through September 2021), the intervention was implemented in one cluster per step at one-month intervals. The first two months of implementation were a transition period, which will not be analyzed. The staggered roll-out occurred over nine months (October 2021 through June 2022), after which 11 months followed during which all clusters were in the transition or intervention condition. The total study duration was planned for 22 months (Fig. 1), completing enrollment April 30, 2023. This manuscript complies with the SPIRIT 2013 checklist (Additional file 1) [21].

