The primary outcome for aim 2 is anticoagulation initiation in eligible patients with AF or atrial flutter at the time of ED discharge to home or within the following 30 days. Eligibility includes an elevated CHA_2_DS_2_-VASc score (≥ 2 in men and ≥ 3 in women) in health plan members not currently taking anticoagulants who are being discharged to home directly from the ED. Current anticoagulation use is defined using EHR data. A patient is considered to be taking oral anticoagulation if (a) any oral anticoagulation prescription was filled in 45 days prior to the index encounter, (b) the supply of a filled prescription would include the index encounter date, or (c) active use of an oral anticoagulant was documented in the medication review during the index encounter or during the 30 days prior. A secondary outcome of aim 2 is electronic consultation of the Anticoagulant Management Service, independent of anticoagulation initiation in eligible patients (defined above).

We will measure use of RISTRA-AF but have not made it a major outcome. Use of the tool may not correlate strongly with use of the management principles that the decision support tool recommends [124]. For example, a physician may use RISTRA-AF to learn that the most effective means of electrically cardioverting an obese patient involves starting with maximal joules combined with manual pressure augmentation. This management principle is easily remembered and may be employed in future cases without recourse to RISTRA-AF. Frequency of tool use would serve as a poor indicator of frequency of optimal electrical cardioversion technique. We observed a similar pattern in prior decision support research on site-of-care decision-making for ED patients with acute pulmonary embolism. Over the course of the 4 years following the initial implementation of the decision support tool, the frequency of safe outpatient management of ED patients with low-risk pulmonary embolism increased though tool use decreased [54]. These two cases (electrical cardioversion of AF and outpatient management of low-risk pulmonary embolism) illustrate why use of our RISTRA tools is optional. We provide these tools to aid clinicians with management decisions if they feel assistance is needed. Use of the CDSS is not mandatory.

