#### Facility-specific monthly engagement by site leads

Local site leads provide their EDs with monthly emails. The content varied month by month, but routinely included commendation to recent local RISTRA-AF users, highlights of overall study progress, and “test your knowledge” questions to keep the AF and atrial flutter education going that began in the training survey. Six months following launch at a study site, site leads presented at an ED meeting a brief overview of the application and fielded questions from their peers. Starting at month 12 (June 2022; Fig. 1), metrics were incorporated into the monthly emails that included three intra-facility comparisons: use of long-acting rate reduction medications, anticoagulation prescribing at time of ED discharge to home, and anticoagulation prescribing in the 30 days following discharge. Each graphic included metrics of the three leading EDs as well as the ED in question (see Additional file 20 for an example).

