#### Analytics and sample size

The aim of the O’CAFÉ trial was to determine whether the intervention reduces hospitalization among eligible ED patients with isolated AF or atrial flutter. We also aimed to determine if the intervention was associated with increased initiation of oral anticoagulants among eligible patients at high stroke risk. To this end, we designed the trial as a superiority trial to determine if intervention sites had better outcomes than control sites.

Analysis of RISTRA-AF effectiveness will be based on comparison of intervention and control groups according to the stepped-wedge cluster randomized pragmatic trial design. All analyses for this stepped-wedge group-randomized trial will be approached using mixed model regression methods. As this is a group-randomized trial and all groups will receive the intervention, all analyses will be done as intent-to-treat. Because the CDSS is available to all ED physicians at each study site and training is given at the site level as part of the intervention initiation, all patients at a given facility will be seen by a physician with access to and knowledge of the CDSS and therefore meet the study definition of “treated.” We will not depend upon CDSS utilization data to identify patients who received CDSS-enhanced care, because as physicians became more familiar with the CDSS content and internalized it, they would be less likely to use the tool during a patient encounter but still deliver care in accordance with the CDSS recommendations. Outcome and predictor measures were derived from the EHR, based on operational processes. We will examine within- and between-cluster correlation over time to elucidate possible correlation structures, including possible time decay in the correlation over time. While intraclass correlation and the number of repeated individuals in our cohort are expected to be low based on pilot study data, we will describe the intraclass correlation and churn rates over time and by cluster. We will use descriptive statistics to examine outcome trends over time overall, by cluster and by intervention status. Following the methods for open cohort stepped-wedge designs with binary outcomes outlined by Li et. al [125], we will use mixed models to allow for clustering with appropriate correlation structures, adjusting for time effects, RISTRA-AF status, and possibly hospital-level fixed effects.

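### The single RISTRA-AF effect mainly estimates months 3 to 5 after launch, so it should not be reported as the effect over the 22 months without a time-since-launch analysis

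*Protocol article*

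**What the plan says.** Analytics and sample size gives the model as mixed regression, "adjusting for time effects, RISTRA-AF status, and possibly hospital-level fixed effects". It names one intervention term and none for time since launch. Outcome trends are to be described over time, by cluster and by intervention status, and facility-specific pre-to-post changes will be reported.

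Trial design fixes the layout. It states that "we had nine study clusters", and it opens the schedule with "After an initial period of three months in which all clusters were in the control condition". Launches were then staggered: "the intervention was implemented in one cluster per step at one-month intervals". On the time just after each launch, the same section says: "The first two months of implementation were a transition period, which will not be analyzed". The total is 22 months.

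Three places bear on whether the effect is steady after launch:

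- Facility-specific monthly engagement by site leads: "Six months following launch at a study site, site leads presented at an ED meeting a brief overview of the application". Monthly teaching emails continue, and comparative performance metrics are added from study month 12.
- Analytics and sample size says that tool use should fall "as physicians became more familiar with the CDSS content and internalized it".
- Outcomes reports that, in the four years after an earlier tool was introduced, "the frequency of safe outpatient management of ED patients with low-risk pulmonary embolism increased though tool use decreased".

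**The concern.** A single status term assumes the same effect in every analysed month. If that holds, how the model weights the months does not matter. If the effect changes with time since launch, the coefficient is a weighted mix of month-specific effects, and the weights come from the design and the correlation structure, not from how many patients were seen in each month. Here the weights fall almost wholly on the first analysed months, and later months can enter with a negative sign.

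The concern is a real one here because what the sites receive is not fixed at launch: a repeat presentation comes at six months and metrics are added later. At stake is the meaning of both primary results. A reader would naturally take the estimate as the effect over the trial, when it is close to an early-exposure effect.

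**Working it through.** **No plan figure to reproduce.** The article gives no figure on this point. Its statement that three clusters give 90% power was not reproduced with its own inputs: nine clusters with monthly time effects give about 27% at the two-sided 2.5% level. The calculator's settings are not shown, and nothing below rests on that figure.

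**Design counts.** Cluster k (k = 1 to 9) launches in month 3 + k.
- Control cluster-months: 3 + 4 + ... + 11 = 63.
- Transition, dropped: 9 × 2 = 18.
- Intervention: 17 + 16 + ... + 9 = 117. Check: 63 + 18 + 117 = 198 = 9 × 22.
- Counting the launch month as 1, months 3 to 5 hold 9 × 3 = 27 of 117 (23%), months 6 to 8 another 27, and months 9 and later 63 (54%).
- The last control cluster-month is study month 11. Only 6 + 5 + 4 + 3 + 2 + 1 = 21 intervention cluster-months have a concurrent control; 96 of 117 have none. The longest exposure with a concurrent control is month 8.

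**Inputs from Analytics and sample size.** Aim 1: 11 encounters per cluster, read as per cluster-month (567 + 460 = 1,027 over 9 × 10 = 90 cluster-months is 11.4); baseline 26.6%; ICC 0.01; cluster autocorrelation 0.47 with decay. Aim 2: 7 encounters, ICC 0.006, autocorrelation 0.356. A 40% baseline is assumed for Aim 2; the weights do not depend on it.

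**Formula.** On cluster-month means, the estimate is the first element of (X'V⁻¹X)⁻¹X'V⁻¹y, with X holding the status term and month effects. For Aim 1, V has between-cluster variance 0.01 × 0.266 × 0.734 and residual variance 0.99 × 0.266 × 0.734 / 11. Weights on intervention cells sum to 1, so the expected estimate is Σ wⱼ δ(eⱼ), where e is months since launch. The comparator is the mean of δ(e) over the 117 cells.

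**Weights by months since launch, monthly time effects**

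| Structure | 3-5 | 6-8 | 9+ |
|---|---|---|---|
| Aim 1, decay | 84% | 17% | -1% |
| Aim 1, nested exchangeable | 93% | 22% | -15% |
| Aim 1, exchangeable | 98% | 24% | -22% |
| Aim 1, decay, fixed site effects | 108% | 24% | -33% |
| Aim 2, decay | 83% | 18% | 0% |

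Rows may not sum to 100% because of rounding. Fixed effects were entered for the nine clusters. With random clusters and decay, months 3 to 5 carry 74 to 84% whether time is linear, quadratic, quarterly or monthly.

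**Consequence under assumed effect shapes** (Aim 1, decay, random clusters; points; the shapes are assumptions and none is in the documents)

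| Shape, maximum 8 points | True average | Estimate | Ratio |
|---|---|---|---|
| Constant | 8.0 | 8.0 | 1.00 |
| 8 × (1 - exp(-e/3)) | 7.2 | 5.8 | 0.81 |
| Linear to month 6 | 7.4 | 5.5 | 0.74 |
| 8 × (1 - exp(-e/6)) | 5.9 | 3.9 | 0.67 |
| 4 through month 6, then 8 | 6.8 | 4.2 | 0.63 |
| Linear to month 12 | 5.7 | 2.8 | 0.49 |
| Linear to month 18 | 4.1 | 1.8 | 0.45 |
| 8 through month 6, then 4 | 5.2 | 7.8 | 1.49 |

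For growing effects the shortfall is therefore 19% (1 - 0.81) to 55% (1 - 0.45). For the 12-month ramp the estimate falls to 2.1 under nested exchangeable, 1.8 under exchangeable and 1.1 with fixed site effects. The last two lie below the smallest true effect in any analysed month, 8 × 3/12 = 2.0.

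**Precision of the alternative.** With indicators for each month since launch, the month 3 to 8 average has a standard error of 5.5 points against 5.2 for the single term (decay). It is 10 to 15% larger under nested or simple exchangeable correlation, and about 38% larger with fixed site effects (8.0 against 5.8).

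**Simplifications.** Linear probability scale; individual autocorrelation and churn ignored; equal cluster sizes.

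**The case against.** A reader might infer that the protocol expects the effect to build and that both primary estimates will therefore be about half the truth. The documents do not support that. No sentence says that the effect on hospitalization or anticoagulation grows with time since launch. The remark on internalized content explains why tool use does not define exposure, and it fits a steady effect equally well. The four-year experience concerns another tool and another condition. The six-month presentation could as well counter waning. Nor does the model assume an immediate effect: the two dropped months are the plan's own allowance for a lag. A shortfall of about half needs a linear ramp of 12 months or more. All of this stands.

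Four further points:

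- **Benchmark.** The whole-trial average is dominated by months without concurrent controls, which any comparison that adjusts for time must weight lightly. Limiting the data to the first 12 to 13 months cuts the linear-ramp shortfall to about 16 to 22%. This stands, and it is why the coefficient needs an accurate label.
- **The alternative is not plainly better.** Under the 12-month ramp the month 3 to 8 average is 8 × 5.5/12 = 3.7 points, still short of 5.7. For that target, the single-term model has the smaller root mean squared error (5.16 to 5.41 against 5.47 to 5.83 points) over the shapes and structures tried. This stands against making the alternative primary.
- **Metrics.** They start in study month 12, when no control months remain. An effect common to all sites would be absorbed by the month effects, and neither analysis would recover it.
- **An unseen analysis plan may hold a time-since-launch term.** It may. But the article does state its model terms, and as stated they give one coefficient for both primary aims.

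**Conclusion.** The point holds in a limited form. As stated, the model yields one effect, constant from month 3 after launch, and about 84% of its weight (83% for Aim 2) rests on months 3 to 5, which are 23% of the analysed intervention cluster-months. Months 9 and later contribute nothing or enter negatively. These weights follow from the design and the working correlation; they need no assumption about how the effect evolves.

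The bias does need one. It is zero for a constant effect, about 19 to 55% understatement for the growing shapes tried with random clusters and decay, larger for the same shapes under the other structures or fixed site effects, and an overstatement if the effect wanes. The direction cannot be settled from the documents. What can be settled is that the coefficient is not the average effect over the 22 months unless the effect is constant, and that the article adds intervention components after launch.

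**What to change.** 1. The constant-effect model may stay primary. State that it mainly estimates the effect about 3 to 5 months after launch, and do not present it as the effect over the 22 months.
2. For both primary aims, pre-specify a key secondary or sensitivity analysis that keeps the month effects and the cluster correlation but replaces the single status term with indicators for months since launch. Report the average over months 3 to 8, the exposure months with concurrent control clusters, and name it as that average.

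The cost is wording and a few model terms; no new data are needed. The price is the modest loss of precision shown above for the month 3 to 8 average, which becomes material only if hospital fixed effects are used. Averaging over all of months 3 to 19 is less precise still (standard error 6.7 to 8.2 points for Aim 1 with random clusters), so it should not be the main summary.

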We estimate that our stepped-wedge design (with nine clusters and 10 steps) will include approximately 3420 adult ED encounters with primary and 972 (30%) with isolated AF or atrial flutter during the 10-month roll-out period. Based on pilot data, we expect at least 567 patients in the usual care condition and 460 patients in the intervention condition with isolated AF or atrial flutter during the 10-month roll-out period. Using preliminary data at the pilot sites and the trial sites, baseline initial hospitalization rate was 26.6%. We estimate a minimally detectable 8% absolute difference in initial hospitalization rate (Aim 1) at a level of 90% power and a 2-sided test at the 2.5% significance level.

We estimated the minimum number of clusters needed to achieve 90% power based on pilot data using the National Institute of Health Stepped-wedge Group Randomized Trial Calculator [126]. We present our most conservative estimates here. For the hospitalization outcome, we assume an average of 11 eligible encounters per cluster, intraclass correlation of 0.01, the cluster autocorrelation of 0.47, and the individual autocorrelation of 0.9 with a discrete-time decay, a churn rate of 0.942 and adjustment for one cluster-level variable (annual ED census) with R [2] of 0.07. We would need only three clusters to see a decrease of 8% in hospitalization rates at 90% power, so we believe that we have adequate power in this analysis, given data from nine clusters over the course of the trial.

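### The Aim 1 power claim (8 points at 90% power, three clusters enough) does not follow from the protocol's own inputs; for the nine-cluster design to be analysed, power is roughly 25% to 41%, depending on the time model

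*Protocol article*

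**What the plan says.** All power figures are in the protocol article under Analytics and sample size. The baseline is given as "baseline initial hospitalization rate was 26.6"%. The headline is "We estimate a minimally detectable 8% absolute difference in initial hospitalization rate (Aim 1) at a level of 90% power", using "a 2-sided test at the 2.5% significance level". Expected roll-out numbers with isolated AF or flutter are at least 567 in usual care and 460 under intervention, for "our stepped-wedge design (with nine clusters and 10 steps".

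A second statement, attributed to a stepped-wedge calculator, assumes 11 eligible encounters per cluster, ICC 0.01, cluster autocorrelation 0.47, individual autocorrelation 0.9 with discrete-time decay, churn 0.942 and one cluster-level covariate with R² 0.07. It ends: "We would need only three clusters to see a decrease of 8% in hospitalization rates at 90% power", from which nine clusters are judged adequate. The inputs are described as the most conservative.

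The design itself is fixed elsewhere. Under Trial design: "we had nine study clusters, which the principal investigator allocated to one of nine sequences", with three baseline months, one launch a month and 22 months in total; also "The first two months of implementation were a transition period, which will not be analyzed". Under Analytics and sample size, the mixed model is described as "adjusting for time effects, RISTRA-AF status, and possibly hospital-level fixed effects".

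**The concern.** This is the only power justification for the first primary aim. The counts look too small for 90% power at a 2.5% level even without clustering. A design with one cluster per sequence also loses much of its information once time is adjusted for and the transition months are removed. If the claim is wrong, a non-significant result would be read as evidence against an 8-point reduction that the analysis had little chance of detecting.

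**Working it through.** **Inputs.** Rates 26.6% and 18.6%, so the variances are 0.266 × 0.734 = 0.1952 and 0.186 × 0.814 = 0.1514, mean σ² = 0.1733. Two-sided 2.5% gives z = 2.241; 90% power gives z = 1.282; their sum is 3.523. Power = Φ(0.08/SE − 2.241). The protocol gives no period for the 11 encounters per cluster. I take it as per cluster-month, because 972 encounters / (9 clusters × 10 months) = 10.8.

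**1. Can the stated figure be reproduced?** The variance of the intervention effect was computed by generalised least squares on cluster-month means. The model had categorical month, a cluster-period effect with ICC 0.01 decaying by 0.47 per month, and individual autocorrelation 0.9 on the retained fraction (1 − 0.942).
- Three clusters in total, 11 per month: 6% to 14% power.
- Nine clusters, 10 periods, no transition months: SE 0.0393, so Φ(2.036 − 2.241) = 42%.
- Three clusters per sequence (27 in all), 10 periods, no transition months: SE 0.0227, so Φ(3.524 − 2.241) = 90.0%.

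Only the third matches the protocol, and the trial has one cluster per sequence.

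**2. Bound from the stated counts.** With no clustering and no time adjustment:
- SE = √(0.1952/567 + 0.1514/460) = 0.02595.
- 0.08/0.02595 = 3.08, and Φ(3.08 − 2.241) = 80% (79% with pooled variance).
- For 90% power: 3.523² × (0.1952 + 0.1514)/0.0064 = 672 per arm.
- Crediting the R² of 0.07 as a full 7% cut in variance: SE = 0.02595 × √0.93 = 0.02503, power Φ(3.196 − 2.241) = 83%.

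**3. Bound for three clusters.** 3 × 11 × 22 = 726 encounters, 363 per arm if split evenly. SE = √(0.3466/363) = 0.0309, and Φ(2.589 − 2.241) = 64%, again ignoring clustering and time.

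**4. Nine clusters as they will be analysed.** 22 months, two transition months dropped per cluster, stated correlations:

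| Time model | SE | Power for 8 points | Detectable at 90% (3.523 × SE) |
|---|---|---|---|
| Categorical month | 0.0507 | 25% | 17.9 points |
| Quadratic | 0.0448 | 32% | 15.8 points |
| Linear | 0.0399 | 41% | 14.1 points |
| None | – | about 88% to 94% | – |

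The last row is a range because runs differed in how the individual autocorrelation was handled. Leaving that term out moves the categorical result from 25% to 28%.

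**5. Hand check with ICC 0 and categorical month.** With k clusters under intervention and c under control in a month, SE = √(σ² / (11 × Σ kc/(k + c))). After the transition months are dropped, only months 6 to 11 contain both conditions: (6 + 10 + 12 + 12 + 10 + 6)/7 = 8.0. SE = √(0.1733/88) = 0.0444, power 33%. Keeping the transition months, months 4 to 11 give 120/9 = 13.3, SE 0.0344 and power 53%. So the low power does not come from the ICC. Months after every cluster has crossed have c = 0 and add nothing in this calculation, which is why 22 months do not rescue power under categorical month.

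**The case against.** The best defence is that the protocol does not fix the form of the time adjustment, so no single power figure belongs to the design. That stands. A reader might take roughly 25% power, or an 18-point detectable difference, as a property of the trial; both depend on categorical month, which the protocol does not specify. Other time-adjusted choices with transition months dropped span about 14% (a t reference with 8 degrees of freedom) to about 45%. None comes near 90%.

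A reader might also infer that the calculation ignored time trends. The documents do not support this: a time-adjusted model returns exactly 90.0% at three clusters per sequence, so time adjustment may well be included. What that match does lack is the transition months.

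Nor can the two power claims be set against each other by scaling 8 points by √3. That rule applies when identical sequences are replicated. Here, moving from three to nine clusters changes the number of sequences, and the SE ratio depends on the layout. The two statements fit together poorly, but that calculation proves nothing.

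Reading 11 as per cluster-month is an assumption. Yet even 114 per cluster-period (the whole roll-out count per cluster, 1027/9) gives three clusters at most about 55% power once time is adjusted for. Finally, the protocol version is dated 13 February 2023 and enrolment was to end on 30 April 2023, so a correction cannot change the size of the trial. It still governs how the result is read.

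**Conclusion.** The concern holds. The 8-point, 90%-power, three-cluster statement is wrong as written. Two parts of this need no mixed-model choice: the stated patient counts give about 80% power at best before clustering and time adjustment, and three clusters give at most about 64%. For nine clusters with transition months dropped and time adjusted, power for 8 points at two-sided 2.5% is about 25% to 41% across categorical, quadratic and linear time. This rests on 11 encounters per cluster-month, the stated correlations and churn, and a normal reference. Power approaches 90% only if time adjustment is dropped, which conflicts with the analysis described. That a per-sequence output was read as a total is a plausible explanation, not an established one, because the calculator output is not in the document.

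**What to change.** Check whether the calculator's three clusters means three per sequence, and correct or remove that sentence accordingly. Re-run the calculation for nine clusters with one per sequence, transition months removed, alpha 2.5% and the time model stated. Replace the 8%/90% claim with the resulting power and detectable difference, giving a range over time models if the model is not fixed. State the period to which 11 encounters per cluster refers. Add that Aim 1 will be interpreted from the confidence interval and that a non-significant result does not exclude an 8-point reduction.

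The cost is one re-run, some rewording and a less favourable stated figure. No extra patients or data are needed.

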Given that only 18% of ED encounters are eligible for stroke prevention action (discharged to home, current KP member, not currently or recently taking oral anticoagulants, and at high risk for stroke), the overall numbers of eligible encounters for the stroke prevention-related outcomes are much smaller. For the primary Aim 2 outcome (any prescription ordered for oral anticoagulation medications within 30 days of the index visit), power is still adequate in this study design to identify changes in rates of prescriptions ordered as small as 5% in the eligible subgroup. Based on pilot data and assuming an average of seven eligible encounters per cluster, intraclass correlation of 0.006, the cluster autocorrelation of 0.356, and the individual autocorrelation coefficient of zero with a discrete-time decay, and a churn rate of 0.984 with no adjustments for cluster-level variables, our nine-cluster design will allow us to identify a 4.9% change in rates of anticoagulant prescription with 80% power.

We anticipate wide variation in practice patterns across our EDs, as we have seen in the management of other conditions [54, 127, 128]. Some EDs might start the trial further from their optimal performance level than others. These EDs may have more potential for practice improvement than others and more to gain from the intervention. To account for this, we will also report facility-specific changes from pre- to post-intervention, anticipating a larger impact at facilities whose pre-intervention practices were in the lower tertile.

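### Aim 2's stated 80% power for a 4.9-point change does not follow from the article's own inputs: recomputed power is about 11–29% for baselines of 10–50% at two-sided 5%

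*Protocol article*

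**What the plan says.** Under Trial design, the article states that "we had nine study clusters, which the principal investigator allocated to one of nine sequences", so each sequence holds one cluster. The first two months after each launch are a transition period that will not be analysed.

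Under Analytics and sample size, the planned analysis is a mixed model that adjusts for time effects. The power calculation refers to "our stepped-wedge design (with nine clusters and 10 steps". For Aim 1 the article gives a baseline rate (26.6%) and a significance level ("a 2-sided test at the 2.5% significance level"). For Aim 2 it gives the correlation inputs: "assuming an average of seven eligible encounters per cluster, intraclass correlation of 0.006, the cluster autocorrelation of 0.356". It also sets the individual autocorrelation to zero under discrete-time decay, takes churn as 0.984 and uses no cluster-level covariate. From these it concludes that "our nine-cluster design will allow us to identify a 4.9% change in rates of anticoagulant prescription with 80% power", and in the sentence before it that "power is still adequate in this study design to identify changes in rates of prescriptions ordered as small as 5" per cent.

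**The concern.** Aim 2 is one of two primary aims, and the article presents it as sensitive to a change of about 5 percentage points. Yet the eligible group is small: "only 18% of ED encounters are eligible for stroke prevention action". That leaves roughly 600 encounters over the roll-out, from nine clusters, and the treatment effect has to be separated from calendar time. A 4.9-point detectable difference looks too small for that amount of information.

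The estimate and its test are unaffected. What is at stake is interpretation. If true power for a 5-point change is low, a null or imprecise Aim 2 result says little about whether such a change occurred, while the published plan tells readers the opposite.

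**Working it through.** **Inputs from the article.** Nine clusters in nine sequences (Trial design). Ten periods, m = 7, ICC = 0.006, cluster autocorrelation (CAC) = 0.356 with discrete-time decay, individual autocorrelation 0, no covariate gain (Analytics and sample size). Seven must mean per cluster per month: 18% × 3420 = 616, and 616 / (9 × 10) = 6.8. Churn was not modelled separately; with individual autocorrelation zero it has almost no effect.

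**Assumptions.** The 4.9% change is read as percentage points; a relative reading makes the absolute change smaller and the claim harder to meet. Baseline p is not stated, so 5% to 50% is shown. The Aim 2 significance level is not stated, so two-sided 5% and 2.5% are shown.

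**Method.** Generalised least squares on cluster-period means, with a fixed effect for each period and a treatment indicator. The covariance between periods s and t of one cluster, per unit outcome variance, is ICC × CAC^|t−s|, plus (1 − ICC)/m on the diagonal. This gives a standard error per unit standard deviation of:

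- 0.1067 with the transition months kept
- 0.1378 with the two transition months per cluster removed

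The outcome variance is the average over the two arms, v = [p(1 − p) + (p + 0.049)(1 − p − 0.049)] / 2. Then SE = 0.1067√v or 0.1378√v, power = Φ(0.049/SE − z), and detectable change = (z + 0.84) × SE, with z = 1.96 (5%) or 2.24 (2.5%).

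**Worked example, p = 30%, 5% level.** v = (0.2100 + 0.2272)/2 = 0.2186. With transition kept, SE = 0.1067 × 0.4675 = 0.0499, power = Φ(0.98 − 1.96) = 16%, and detectable change = 2.80 × 0.0499 = 14.0 points. With transition removed, SE = 0.0644, power = Φ(0.76 − 1.96) = 12% (11.5% unrounded), and detectable change = 18.0 points.

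**Results.** Power for 4.9 points, with the change detectable at 80% power in brackets:

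| Baseline | 5% level, transition kept | 5% level, transition excluded | 2.5% level, transition excluded |
|---|---|---|---|
| 5% | 42% (7.8) | 27% (10.1) | 19% (11.1) |
| 10% | 29% (9.8) | 19% (12.7) | 12% (14.0) |
| 20% | 20% (12.5) | 13% (16.1) | 8% (17.7) |
| 30% | 16% (14.0) | 12% (18.0) | 7% (19.9) |
| 50% | 15% (14.9) | 11% (19.3) | 6% (21.2) |

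The stated 80% appears in no row. Above 50% the pattern mirrors; power is about 41% at a 90% baseline (5% level, transition kept). Normal quantiles are used throughout, which favours the design over a t reference with few degrees of freedom.

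**What baseline would rescue the figure?** At the 5% level with transition kept, 80% power needs SE = 0.049/2.80 = 0.0175, so v = (0.0175/0.1067)² = 0.0269. At p = 0.4%, v is already (0.0040 + 0.0502)/2 = 0.0271. The baseline would have to lie below about 0.4%, or at the mirror-image extreme near 95%.

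**Other routes to 80%.**

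- Using all 22 months leaves both standard errors unchanged to four decimals. Once period effects are fitted, months in which every cluster is in the same condition add almost nothing.
- A plain two-proportion test of 315 against 315 (9 × 10 × 7 = 630 encounters), ignoring clustering and time, gives 65% at a 5% baseline, 31% at 20% and 23% at 50%.

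**Cross-check on Aim 1**, where baseline and level are stated. The article says three clusters suffice for an 8-point decrease at 90% power. The same method with m = 11, ICC 0.01 and CAC 0.47, at the 2.5% level with transition kept, gives 45% for nine clusters, 78% for 18 (two per sequence) and 92.5% for 27 (three per sequence). Three clusters in total give about 6–10%.

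**The case against.** The article condenses a fuller protocol, and a missing Aim 2 baseline or significance level may simply be stated there. That stands: the omission is not itself the fault. But it does not rescue the claim, because no plausible value of either quantity yields 80% power under the planned model.

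It can also be said that dropping time adjustment and using 22 months does reach 4.9 points. It does, but only with a baseline near 5% or 90% (about 88% power there, falling to 70% at a 10% baseline), and it contradicts the time-adjusted analysis in the same section.

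Two stronger readings are tempting.

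- A reader might infer that nine was entered as clusters per sequence, so that the figure really describes 81 clusters. This is possible, and the Aim 1 three-cluster figure fits the same pattern, but it is unproven. The match depends on choosing an unstated baseline and level and on keeping the transition months: 81 clusters then detect 4.9 points at a 40% baseline at the 5% level, or at 25% at the 2.5% level. With transition excluded, 81 clusters detect 6.0–6.4 points at baselines of 30–50% at the 5% level, which is no match.
- A reader might infer an inflated familywise error, with Aim 1 tested at 2.5% and Aim 2 at 5%. Nothing says Aim 2 is tested at 5%, and a 2.5% level is equally consistent with 5% split over two primary aims.

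Finally, roll-out ended in June 2022 and the number of clusters is fixed, so nothing in the design can be changed. This limits the remedy to correcting the statement.

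**Conclusion.** The claim of 80% power for a 4.9-point change does not reproduce from its own inputs. At two-sided 5% and baselines of 10–50%, power is about 15–29% with transition months kept (detectable change about 10–15 points) and about 11–19% with them excluded as the article plans (about 13–19 points). At 2.5% with transition excluded, it is about 6–12% (about 14–21 points).

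This rests on the assumed baseline range, a linear mixed model with categorical periods, seven encounters per cluster-month, and variance averaged over the arms at a 4.9-point difference. Using control-arm variance alone would flatter the design at low baselines (37% instead of 27% power at a 5% baseline with transition excluded) without changing the conclusion. The cause of the discrepancy cannot be established from the article.

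**What to change.** Recompute Aim 2 power and detectable difference with one cluster per sequence, the transition cells removed, and the pilot baseline prescribing rate and Aim 2 significance level actually used. State both values in the text. Replace the 4.9%/80% statement with the result, and delete the statement that changes as small as 5% can be identified. The replacement should carry the pilot rate, not a baseline assumed in this review. It would be sensible to check in the same run how the number of clusters was entered for the Aim 1 three-cluster figure.

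The cost is one rerun and a few reworded sentences, with no change to conduct or analysis. The downside is a less favourable stated figure.
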